### Exclusion criteria

Patients with any of the following conditions will be excluded: (1) concurrent urinary tract infection, malignant tumor, stone.; (2) Patients with previous history of epileptic seizure, central nervous system disease, mental disease, and psychological disease; (3) Patients with cranial and sacrococcygeal metal implants, increased intracranial pressure, heart disease, cardiac pacemaker, drug pump, and unable to receive MS treatment; (4) Patients who are taking tricyclic antidepressants, neuroleptics, or have a family history of epilepsy; (5) Dysfunction of urination caused by other diseases; (6) Patients who had undergone urethral sphincterotomy or cystostomy; (7) Patients with unstable vital signs, hemodynamic instability, skin damage, and bleeding tendency; (8) Pregnant and lactating women.

### Drop out criteria

Once subjects have signed the informed consent form and have been screened and are eligible for entry into the clinical trial, cases that do not complete all clinical trial visits, regardless of the reason, will be considered to be disengaged from the clinical trial as long as they do not complete the clinical trial. If the patient develops urinary tract infection and is given the appropriate treatment, and the infection can be controlled within 1 week, the patient will be allowed tocontinue to complete the experiment; Patients who terminate the trial because their condition has resolved and no further treatment is required will not be included in the shedding.

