### Sample size calculation

According to published literature (33) the mean post-intervention residual urine volume in the four groups A, B, C, and D were expected to be 302.6, 56, 107.2, and 179, respectively, with a standard deviation of 160.4. The degree of certainty 1−β = 0.90, test level *α* = 0.05, group A:B:C:D = 1:1:1:1 and sample size estimation will be performed using PASS 15 software according to the following equation.

$$n=\Psi^{2}\left[\overset{k}{\underset{i=1}{\sum }}{s_{i}}^{2}/k\right]/\left[\overset{k}{\underset{i=1}{\sum }}{\left({\bar{X}}_{i}-\bar{X}\right)}^{2}/\left(k-1\right)\right]$$

According to the predefined parameters, the minimum required samples for groups A, B, C and D were all 12 cases after the calculation of residual urine volume using One-Way Analysis of Variance F-Tests under the Means menu of PASS 15 software. Considering the lost rate of 20%, it is expected that 15 cases will be included in groups A, B, C, and D in this study, and a total of 60 cases will be included, which can ensure the accuracy and scientific accuracy of the study results.

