### Randomization and blinding

Randomization of included patients based on length of stay will be performed using the random number table method. Throughout the study, all investigators and subjects will be unaware of the allocation of interventions, Outcome evaluators and data analysts will be blinded, and subjects will be randomly assigned to groups by persons unrelated to the trial. Opaque closed envelopes containing sequence numbers used for allocation concealment will be identified with different numbers. Once the sequences is generated, the envelopes will be placed in a secure place in numerical order and the paper containing the corresponding group information will be placed in the envelopes. Sequence generation and production will be performed by rehabilitation physicians not involved in this study.

An experienced blinding rehabilitation physician or therapist will perform an initial assessment of enrolled patients and an assessment after 2 weeks of treatment. In the event of a serious adverse event, emergency unblinding will be performed and the involved subject will be removed from the trial protocol. When the experiment is complete, the statisticians will have four sets of data.

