### Safety and adverse effects of rFMS

RFMS is generally noninvasive and safe, but occasionally causes transient headache and fatigue (39). Adverse events will be managed as follows: (1) If informed of discomfort, the investigator will immediately stop treatment, assess the patient’s vital signs, type and degree of discomfort, and then administer appropriate treatment. (2) All adverse events will be recorded and reported to the principal investigator and the ethics committee, who will jointly decide whether the patient is fit to continue participation.

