### Withdrawals

Participants may withdraw from the study due to serious adverse events (such as seizures or cerebrovascular accidents) or other personal factors (participant refusal to continue treatment, etc.).

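### The drop-out and adverse-event rules contradict each other and merge stopping treatment with leaving the trial, so primary-outcome data could be lost in an outcome-dependent way of unknown direction

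*Protocol article*

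**What the plan says.** All references are to the protocol article.

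- **Drop out criteria, general rule.** "cases that do not complete all clinical trial visits, regardless of the reason, will be considered to be disengaged from the clinical trial".
- **Drop out criteria, last sentence.** "Patients who terminate the trial because their condition has resolved and no further treatment is required will not be included in the shedding". By context, shedding means being counted as a drop-out.
- **Drop out criteria, infection.** If a urinary tract infection is treated "and the infection can be controlled within 1 week, the patient will be allowed tocontinue to complete the experiment". What happens otherwise is not written.
- **Randomization and blinding.** After a serious adverse event, "emergency unblinding will be performed and the involved subject will be removed from the trial protocol".
- **Safety and adverse effects of rFMS.** All adverse events go to the principal investigator and the ethics committee, "who will jointly decide whether the patient is fit to continue participation".
- **Withdrawals.** "Participants may withdraw from the study due to serious adverse events", among other reasons.
- **Primary outcome.** Residual urine is measured by ultrasound on the first day of treatment and the first day after it. Outcome measures puts the second assessment 2 weeks after treatment starts. Study design and the note to Table 1 put it 2 weeks after treatment.
- **Sample size calculation.** At least 12 per group are needed. With a 20% loss allowance this becomes 15 per group, 60 in all.

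**The concern.** Two sets of sentences cannot be applied together.

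The first set is in Drop out criteria. A patient whose retention resolves in week 1 and who then leaves has not completed all visits. The general rule admits no exception for cause, so this patient is a drop-out; the last sentence says the opposite. Escaping the drop-out label also does not give the patient a primary-outcome value. The exemption describes people who end the trial, and it does not say whether they are scanned again, or when. The three descriptions of the post-treatment assessment make this worse, because for someone who stops on day 5 they can fall on different days.

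The second set concerns serious adverse events: removal in one section, a joint decision in another, optional withdrawal in a third.

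Both sets treat the end of stimulation as the end of participation. The reasons (recovery, a serious adverse event) arise after randomisation and can depend on treatment and outcome. If such patients have no post-treatment scan, the patients compared are no longer those randomised. With 15 per arm, 20% is only three patients (0.20 × 15 = 3). A later statistical analysis plan can name an analysis set, but it cannot recover an ultrasound that was never done.

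**Working it through.** **1. The plan's own figure.** Inputs from Sample size calculation: means A 302.6, B 56, C 107.2, D 179; SD 160.4; α = 0.05; power 0.90; equal allocation. That section gives no unit; mL is assumed from the eligibility criteria.

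- Grand mean = (302.6 + 56 + 107.2 + 179)/4 = 161.2.
- Sum of squared deviations = 141.4² + 105.2² + 54.0² + 17.8² = 34,293.84.
- Noncentrality λ = n × 34,293.84/160.4² = 1.333n, with 3 and 4(n − 1) degrees of freedom.
- Power of the one-way ANOVA F test: 0.8785 at n = 11 and 0.9096 at n = 12, so the minimum is 12.
- 12/(1 − 0.20) = 15 per group; 4 × 15 = 60.

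The stated figures are reproduced. This point does not change the sample size.

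**2. The rules applied to the same patient.**

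| Patient | Rule 1 | Rule 2 | Compatible? |
|---|---|---|---|
| Resolves early, leaves | Drop out criteria, general rule: drop-out | Drop out criteria, last sentence: not a drop-out | No |
| Serious adverse event | Randomization and blinding: removed | Safety section: joint decision; Withdrawals: optional | No |

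**3. What leaving out resolvers could do (illustration).** The article gives no resolution rate, so shares r of 10% and 20% are assumed. Suppose a share r of an arm with mean μ resolves with a volume of about 0 and is left out. Then μ = r × 0 + (1 − r) × m, so the remaining mean is m = μ/(1 − r), a rise of μr/(1 − r). Because volumes cannot be negative, this is the largest rise possible for that r. Arm A is held at 302.6.

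| Arm | Planned mean | Rise, r = 10% | Rise, r = 20% | Planned gap to A | Gap, r = 10% | Gap, r = 20% |
|---|---|---|---|---|---|---|
| B | 56 | 6.2 | 14.0 | 246.6 | 240.4 | 232.6 |
| C | 107.2 | 11.9 | 26.8 | 195.4 | 183.5 | 168.6 |
| D | 179 | 19.9 | 44.8 | 123.6 | 103.7 | 78.9 |

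The comparisons between active arms have smaller planned gaps: B-C 107.2 − 56 = 51.2 and C-D 179 − 107.2 = 71.8. If only B loses 20% this way, B-C becomes 107.2 − 70 = 37.2. If only C does, B-C becomes 134 − 56 = 78.0. The gap can shrink or grow.

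**4. The opposite direction.** If the patients left out have poor outcomes, with a mean w above μ, the remaining mean falls by r(w − μ)/(1 − r). Taking w one planning SD above μ as an assumption, the fall is 160.4 × 0.1/0.9 = 17.8 at 10% and 160.4 × 0.2/0.8 = 40.1 at 20%. This flatters the arm that loses them.

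**The case against.** The strongest reply is that a general rule followed by an exception is ordinary drafting, and that the exception protects resolvers. The second half of that stands: the last sentence of Drop out criteria does not remove resolved patients. A reader might infer that it does, and the text does not support this. The first half only partly helps, because a rule that applies whatever the reason leaves no room for an exception by reason, and the exemption does not say what value these patients contribute.

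Other inferences that the document does not support:

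- **A completer analysis.** Going from 12 to 15 is routine inflation for loss whatever the analysis set. No section says that drop-outs are left out, and naming an analysis set may properly be left to a statistical analysis plan that is not shown. That omission is not the point here.
- **Removal for uncontrolled infection.** This is implied by the one-week condition but not written.
- **Bias against the most effective arm.** That needs resolvers to be left out and to be more frequent in that arm. Losing poor outcomes acts the other way.
- **Larger shifts from a normal model.** Cutting the lowest 10% or 20% of a normal distribution with SD 160.4 gives shifts of about 31 or 56 mL. In B, however, the 10% cut lies at 56 − 1.282 × 160.4 ≈ −150 mL, and in C and D it is also negative (about −98 and −27). The limits in the table above apply instead.

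It is also fair to say that the ultrasound is scheduled for all four groups and no section waives it for early resolvers, and that removal from the trial protocol need not mean discarding data. The document is therefore ambiguous on these patients; it does not order that they go unmeasured.

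**Conclusion.** The point holds in this form. Drop out criteria contradicts itself on early resolvers and leaves their primary-outcome value open. The statements on serious adverse events in Randomization and blinding, in the safety section and in Withdrawals do not agree. Stopping treatment and leaving the trial are treated as one event, for reasons linked to outcome. Outcome-dependent loss of the primary outcome is therefore possible, and its direction cannot be determined from the document.

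The possible size is uneven. Under the assumed shares, A-B hardly moves, while A-D, which concerns the combined arm hypothesised to be better than either single site, could lose about 20 of 123.6 at 10% or 45 at 20%. These figures rest on assumed shares, resolvers at about 0 mL being left out, and no loss in arm A. They are upper limits for leaving out resolvers from that one active arm, and they do not forecast what will happen. The point should be corrected, but it does not undermine the design or the sample size.

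**What to change.** 1. Reconcile the two sentences in Drop out criteria, so that a patient who resolves early has one status.
2. Reconcile the serious-adverse-event statements in Randomization and blinding, Safety and adverse effects of rFMS, and Withdrawals. Which clinical rule applies is for the investigators; this review takes no view on it.
3. Separate stopping stimulation from leaving the trial throughout.
4. State that every randomised patient, including early resolvers and those off stimulation, has residual urine measured at the scheduled post-treatment time unless consent is withdrawn. The differing descriptions of that time must be made one, defined so that it can be applied to a patient who stopped early.
5. State that these patients are analysed in their assigned arm, with completers as a sensitivity analysis.

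The cost is a few sentences of protocol text and a few already scheduled ultrasounds in patients who stopped early, some of whom may have to return for them. The sample size is unchanged.

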### Sample size calculation

According to published literature (33) the mean post-intervention residual urine volume in the four groups A, B, C, and D were expected to be 302.6, 56, 107.2, and 179, respectively, with a standard deviation of 160.4. The degree of certainty 1−β = 0.90, test level *α* = 0.05, group A:B:C:D = 1:1:1:1 and sample size estimation will be performed using PASS 15 software according to the following equation.

$$n=\Psi^{2}\left[\overset{k}{\underset{i=1}{\sum }}{s_{i}}^{2}/k\right]/\left[\overset{k}{\underset{i=1}{\sum }}{\left({\bar{X}}_{i}-\bar{X}\right)}^{2}/\left(k-1\right)\right]$$

According to the predefined parameters, the minimum required samples for groups A, B, C and D were all 12 cases after the calculation of residual urine volume using One-Way Analysis of Variance F-Tests under the Means menu of PASS 15 software. Considering the lost rate of 20%, it is expected that 15 cases will be included in groups A, B, C, and D in this study, and a total of 60 cases will be included, which can ensure the accuracy and scientific accuracy of the study results.

### Recruitment strategies

Eligibility screening of SCI patients will receive rehabilitation treatment at the Department of Rehabilitation Medicine, The First Affiliated Hospital of Ganan Medical University, from January 2023 to December 2023 will be conducted in strict accordance with the inclusion and exclusion criteria mentioned above, those patients who pass the eligibility screening will be included in the randomized trial. If a participant withdraws midway through the trial, the reason for withdrawal will be carefully documented. During the recruitment process, potential participants will be briefed on the intervention approach, study schedule and study procedures. The Standard Protocol Items: SPIRIT table for enrolment, interventions, and assessments is presented in Table 1.

**Table 1 tab1:** Schedule of enrollment, assessments, and interventionis in the RCT.

	Screening	Baseline evaluation	0	2 week	Post evaluation
**Enrollment**					
Informed consent	×				
Demographic information	×				
Vital sign	×				
Medical history	×				
Eligibility assessment	×				
Random allocation		×			
**Allocation Assessments**					
fNIRS		×			×
Residual bladder urine volume		×			×
Urination diary		×			×
Glazer assessment		×			×
QOL		×			×
Interventions					
Sham group					
M1 RMS group					
S3 RMS group					
M1 + S3 group					

“×” indicates at which point of the RCT the respective assessments will take place 0: time of the start of treatment baseline evaluation: one day before treatment post evaluation: 2 weeks after treatment and evaluation.

### Randomization and blinding

Randomization of included patients based on length of stay will be performed using the random number table method. Throughout the study, all investigators and subjects will be unaware of the allocation of interventions, Outcome evaluators and data analysts will be blinded, and subjects will be randomly assigned to groups by persons unrelated to the trial. Opaque closed envelopes containing sequence numbers used for allocation concealment will be identified with different numbers. Once the sequences is generated, the envelopes will be placed in a secure place in numerical order and the paper containing the corresponding group information will be placed in the envelopes. Sequence generation and production will be performed by rehabilitation physicians not involved in this study.

An experienced blinding rehabilitation physician or therapist will perform an initial assessment of enrolled patients and an assessment after 2 weeks of treatment. In the event of a serious adverse event, emergency unblinding will be performed and the involved subject will be removed from the trial protocol. When the experiment is complete, the statisticians will have four sets of data.

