## Methods and study design

### Study design

This trial is a pilot single-center, prospective, double-blind, randomized, controlled study (e.g., Figure 1), and 60 patients with urinary retention after SCI will be selected. According to the sequence of hospitalization time, patients will be randomly assigned to group A (sham stimulation), group B (rTMS of Bilateral M1), group C (rMS of S3 nerve root), and group D (rTMS of Bilateral M1 + rMS of S3 nerve root) in a 1:1:1:1 ratio, combined with conventional rehabilitation treatment.The intervention measureswill be once a day, 20 min, 5 times a week, and the whole experiment cycle will last 2 weeks (10 times in total). Study time point: bladder residual urine volume, brain fNIRS, urination diary, pelvic floor surface electromyography Glazer assessment and quality of life (QoL) assessment will be performed 1 day before treatment and 2 weeks after treatment, respectively. A flowchart overview of the study is presented in Figure 1.

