### Research group and intervention

1. In this experiment, Wuhan Ired MagTD 60 magnetic stimulator will Be used, The stimulation coil will select a circular coil, and The stimulation parameters will Be selected As follows: the stimulation frequency will choose 20HZ, The intensity will select 80–120% resting motion threshold (RMT), The stimulation time will last for1s, The interval will last for9s, and a total of 20 Min will Be stimulated once a day, 5 times a week for 2 weeks.

Group A: in the sham stimulation group, subjects will remain in a supine position, and the stimulation coil will be chosen to be a circular coil with the stimulation site 2 cm in front of the vertex, which is not discharged, and another “8” coil rotated and placed under the subject’s pillow to avoid scalp stimulation (34).

Group B: rTMS of Bilateral M1, The patients will beseated or supine, wore anatomic positioning caps, and selected M1 region according to the international EEG 10–20 system (25), and the handle willpointed to the anteromedial aspect of the sensorimotor cortex on one side, the neck will beimmobilised to avoid head movement and the coil was placed close to the scalp with the central stimulation point tangential to the scalp. To ensure the accuracy of the MS site, the patient’s RMT will be determined by a single manual stimulation, and alternating left and right stimulation was given for 10 min each according to the stimulation parameters.

Group C: rMS of S3 nerve root, the patient will beplaced in prone position, and the stimulation site will select the S3 nerve root region (about the midpoint of the upper sacral edge and the tailbone line to the left and right). The center of the coil will be as close to the surface of the sacrum as is appropriate. Stimulation will be determined by bilateral toe movements or pronounced anal contractions (35), identified as RMT, and then rMS will be given based on the stimulation parameters.

Group D: dual-target stimulation of bilateral M1 and S3 sacral nerve roots will be performed at the same time.

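### The protocol claims that all investigators and subjects are blind, but its arms differ in coil site and only the head has a sham: operators cannot be blind, and patients at most between groups A and B

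*Protocol article*

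**What the plan says.** The Study design section gives the label: "This trial is a pilot single-center, prospective, double-blind, randomized, controlled study". The Randomization and blinding section widens it: throughout the study, "all investigators and subjects will be unaware of the allocation of interventions". The same sentence then adds, as a separate item, "Outcome evaluators and data analysts will be blinded". The claim about investigators and subjects is therefore additional to assessor and analyst blinding. No treating operator is exempted.

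The section Research group and intervention describes the arms:

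- **Group A (sham):** "in the sham stimulation group, subjects will remain in a supine position". A circular coil is held at the head, "with the stimulation site 2 cm in front of the vertex, which is not discharged". A second, figure-eight coil is turned and put under the pillow.
- **Group B:** seated or supine, positioning cap, neck held still, single pulses to find the motor threshold, then active stimulation of left and right M1, 10 minutes each.
- **Group C:** "the patient will beplaced in prone position", with an active coil at the S3 region. Threshold is found from toe movement on both sides or marked anal contraction.
- **Group D:** M1 and S3 stimulated at the same time. Posture is not stated.

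Under Recruitment strategies, "potential participants will be briefed on the intervention approach, study schedule and study procedures".

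**The concern.** The article makes a positive statement about blinding and then describes procedures that defeat it. This is not a detail left to a fuller document.

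The Discussion says that the sham group is there to validate the effect of magnetic stimulation. A reader who takes the double-blind label at face value will assume that expectation and differences in care are controlled in every comparison with sham, and in the comparison of combined with single-site stimulation that forms the second hypothesis. If patients can see which region is treated, and operators know exactly what is delivered, blinded assessment at the end cannot remove differences that arose during the two weeks of treatment. The Limitations section does not mention blinding.

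**Working it through.** The point is one of consistency, so the check sets the sections side by side. The only figures used are the group sizes. The Sample size section plans 12 per group, raised for 20% loss to 12 / (1 − 0.20) = 15, and 4 × 15 = 60. With the stated means and SD, one-way ANOVA power is 0.879 at 11 per group and 0.910 at 12, so the plan's figure reproduces. Blinding does not change it.

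**Step 1: what the treatment set-up shows.**

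| Arm | Coil at head | Coil at sacrum | Posture |
|---|---|---|---|
| A | yes, undischarged (second coil under pillow) | none | supine |
| B | yes, active | none | seated or supine |
| C | none | yes, active | prone |
| D | yes, active | yes, active | not stated |

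**Step 2: operators.** To treat any patient, the operator must choose the site and decide whether the coil discharges. In B and C the operator also finds a threshold by watching for a response. These choices identify the arm, so the operator cannot be unaware. This does not depend on what patients are told.

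**Step 3: patients.** A patient can tell head, sacral and dual-site treatment apart by where the coil is. In C, the prone position and the evoked response add to this. Between A and B, the site is the head in both and the posture can be supine in both. The cap, threshold pulses and active scalp stimulation in B may still give the arm away, but a patient new to the technique may not notice.

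**Step 4: which contrasts are affected.** Four arms give 4 × 3 / 2 = 6 pairs. Two arms have a sacral coil (C, D) and two do not (A, B), so 2 × 2 = 4 pairs differ in that respect: A-C, A-D, B-C and B-D. Of the remaining two, C-D shares an active sacral coil but only D has a coil at the head, since C has no head sham. That leaves A-B as the one pair in which patient blinding could hold.

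**Step 5: which outcomes are exposed.**
- Quality of life is the patient's own 0-6 rating of satisfaction. The exposure is direct.
- The diary counts voids, catheterisations and volumes over three days of ordinary care. The exposure is clear.
- Residual urine, the primary outcome, is measured by ultrasound, but only after the patient has tried to empty the bladder unaided. The exposure is possible.

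**The case against.** **The article is a condensed text and the operator may not count as an investigator.** The blinding sentence says all investigators and exempts nobody, and the safety section has the investigator stopping treatment when discomfort is reported. Even on a narrow reading of the word, the claim about subjects remains.

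**Outcome assessment is blinded.** This stands. The Outcome measures section assigns all evaluations to the same uninformed therapist and physician, and nothing in the arm descriptions contradicts that. It is the part of the claim worth keeping.

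**Sham at the head is reasonable for group B.** This also stands. Groups A and B can share posture and region, so it would be wrong to say that every arm has its own site and posture, or that patients can identify every arm.

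**Seeing a sacral coil does not tell the patient that it is active.** A reader might infer that all 30 patients in C and D (15 + 15) know for certain that they receive active sacral treatment. The document does not support certainty. That inference requires knowing that no arm has a sacral sham, and the content of the briefing and consent form is not shown. An evoked toe or anal response makes unmasking plausible, not certain.

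**Harm to the primary outcome is conjecture.** In part this stands. Catheterisation frequency is tied to bladder capacity and residual volume in all arms, and the text does not say who decides it or who delivers bladder training. An effect of expectation on ultrasound residual volume is possible, but nothing in the document quantifies it.

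**Conclusion.** The contradiction holds. The claim that all investigators are unaware cannot be carried out as written, and the claim for subjects is not credible between treatment sites. Patient blinding is possible at most between A and B. The four contrasts that differ in the presence of a sacral coil, out of six, are not protected by it.

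This rests on two assumptions: that the arms are run as described, and that the coil's position is apparent to the patient.

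A reader might go further and conclude that the bias favours the arms with a sacral coil, or that the residual-urine result is invalid. Neither follows. The document gives nothing from which to derive the direction or the size of a bias, and assessor blinding remains feasible. What changes is the strength of the conclusions, above all for quality of life and the diary.

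**What to change.** 1. **Reconcile** the Study design, Randomization and blinding, and Research group and intervention sections. State that outcome assessors and analysts are blinded, that operators are not, and that patients are blinded at most between A and B. Remove the statement that all investigators and subjects are unaware. Cost: wording only.
2. **Record each patient's guess of allocation** at the post-treatment evaluation, with a don't-know option. Collect it after the outcome measurements and not through the blinded assessor, so that asking does not unblind the assessment. Cost: one question.
3. **Interpret A-C, A-D, B-C and B-D as not patient-blinded** when reporting, above all for quality of life and the diary, and add this to the Limitations. Make no patient-blinding claim for C-D either. Cost: wording only.

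A matched sham at both sites in every arm is an option for the sponsor to consider, not a required change. An undischarged sacral coil would not produce the response used to set the threshold. Simultaneous stimulation in D, with no stated posture, would also have to be worked into a common procedure. The article names the stimulator model but not the number of devices, coils or operators, so the cost of this option cannot be judged from it.

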## Outcome measures

Outcome measures will be evaluated at 1 day before intervention and 2 weeks after the start of treatment. All evaluations will be conducted by the same uninformed therapist and rehabilitation physician.

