### Primary outcome

The most important evaluation index is the residual urine volume of the bladder, the residual urine volume of the bladder can intuitively show the improvement of the urination function of patients with urinary retention. The main way is to measure the residual urine volume of the urinary system color ultrasound of the four groups of patients on the first day of treatment and the first day after treatment. Prior to the examination, the patient first attempts to empty the urine without external force or manipulation, and then a urinary ultrasound will be performed immediately. During the examination, the patient will be asked to lie flat on their back with the probe located in the midline above the pubic symphysis. Each measurement will scan the bladder in both the sagittal and transverse planes and measure the bladder capacity at this point to get an idea of the patient’s residual urine volume. The smaller the residual urine volume, the lower the degree of urinary retention.

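### The serious adverse event rule makes unblinding and removal automatic, with no condition of clinical need, and conflicts with the joint decision on continuation that the safety section sets for all adverse events

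*Protocol article*

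**What the plan says.** Two sections of the protocol article tell staff what follows a serious adverse event.

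- **Randomization and blinding:** "In the event of a serious adverse event, emergency unblinding will be performed and the involved subject will be removed from the trial protocol". Both verbs are unconditional. Relatedness to stimulation and the clinical need to know the allocation are not mentioned.
- **Safety and adverse effects of rFMS:** "All adverse events will be recorded and reported to the principal investigator and the ethics committee". This covers adverse events of every grade. Continuation is then a case-by-case judgement by these two parties, described as those "who will jointly decide whether the patient is fit to continue participation".

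A third section, Withdrawals, mentions serious events in another role: "Participants may withdraw from the study due to serious adverse events (such as seizures or cerebrovascular accidents) or other personal factors". It lists reasons why a participant might leave.

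Three other statements bear on the consequences.

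- Outcome measures relies on blinded assessment: "All evaluations will be conducted by the same uninformed therapist and rehabilitation physician".
- Primary outcome places the residual urine ultrasound "on the first day of treatment and the first day after treatment", so there is one post-treatment measurement. Table 1 likewise shows a single post evaluation.
- Research group and intervention gives three arms 20 Hz stimulation, while the sham coil is one "which is not discharged".

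**The concern.** A serious event is the moment when staff most need a single instruction. Here one section removes the patient outright, and another asks two parties to judge whether the patient is fit to go on. Both cannot be followed as written.

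Two features of the automatic rule deserve attention even if it is taken to prevail.

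- **Unblinding without need.** Stopping stimulation is a sound precaution and does not require the code. Opening the code whenever an event is classed as serious gives up blinding in cases where care would be the same without it.
- **Unclear scope of removal.** The wording may mean only that stimulation stops, or that the patient leaves the trial. On the second reading the primary measurement may be lost. Only three of the four arms receive active stimulation, so such a loss could be related to treatment.

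**Working it through.** **1. The two rules side by side**

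| | Randomization and blinding | Safety and adverse effects of rFMS |
|---|---|---|
| Applies to | serious adverse events | all adverse events |
| Continuation | subject is removed | principal investigator and ethics committee decide |
| Code | opened every time | not mentioned |

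Serious events fall in both columns, and the continuation row differs. No section ranks the two rules.

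**2. The route to a lost outcome.** All of these must hold: a serious event occurs before the post-treatment ultrasound; removal is taken as leaving the trial; and the patient could otherwise have attended. Bias further requires that the event be related to residual volume. Some of these patients could not attend under any rule.

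**3. The planned sample size, as a reference.** From the section on sample size calculation: means 302.6, 56, 107.2 and 179; SD 160.4; alpha 0.05; power 0.90; 20% loss.

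- Grand mean = 161.2. Sum of squared deviations = 141.4² + 105.2² + 54.0² + 17.8² = 34,293.84.
- Noncentrality λ = n × 34,293.84 / 160.4² = n × 1.333.
- Noncentral F power with four groups: 87.9% at n = 11 and 91.0% at n = 12. The minimum is 12, and 12 / (1 − 0.20) = 15 per arm. The plan's figures reproduce.

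**4. Power if one patient is lost from one active arm.** Power is 96.5% with 15 in every arm. One lost from B gives 96.1%, from C 96.4%, from D 96.5%. Even 12 in every arm, the planned loss, leaves 91.0%.

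**5. Shift in an arm mean (illustration).** Assume that the lost patient ranks highest of 15 on a marker with correlation r to residual volume. The expected maximum of 15 standard normal values is 1.736, so

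shift = −r × 1.736 × 160.4 / 14.

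- r = 0: 0 mL.
- r = 0.25: −5.0 mL.
- r = 0.5: −9.9 mL.

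The smallest planned difference between an active arm and sham is 302.6 − 179 = 123.6 mL, so these shifts are 4% and 8% of it.

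**6. Chance that the rule is invoked.** The protocol gives no serious event rate. For assumed rates p per patient, the chance of at least one event in an arm of 15 is 1 − (1 − p)^15:

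- p = 0.5%: 7.2%.
- p = 1%: 14.0%.
- p = 2%: 26.1%.

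Weighting the shift by this chance gives 0.072 × 5.0 = 0.4 mL at the low end and 0.261 × 9.9 = 2.6 mL at the high end, or 0.3% to 2.1% of 123.6 mL.

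**The case against.** The best defence is that the specific rule governs the general one. The randomization section deals with serious events. The safety section opens with headache, fatigue and discomfort, so its decision on continuation fits milder events. The word emergency also hints at an urgent need. This is a reasonable reading and may be what the authors meant. It does not remove the overlap: the safety section says all adverse events, makes no exception, and no text says which rule yields. Nor does the defence add a condition of need to the unblinding step, or say what removal covers.

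Some stronger inferences are tempting, and here the defence is right.

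- **A third conflicting rule.** A reader might set the Withdrawals wording against mandatory removal. That section only lists possible reasons for leaving and is not an instruction to staff.
- **A breach of assessor blinding.** A reader might infer that the assessor learns the allocation. Nothing says so. The article states that evaluators and analysts are blinded, and who is told after an emergency unblinding is operational detail that a condensed article may leave to the full protocol.
- **A barred measurement.** No section forbids the post-treatment ultrasound after a serious event. The drop-out criteria label patients who miss visits; they do not prevent measuring them.
- **A material bias.** The figures do not show one. The event rates, the correlation and the choice of the highest of 15 are all assumed, and the last is an extreme case.

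**Conclusion.** The point holds as a conflict between two stated rules, together with an unblinding step that carries no condition of clinical need. Because the objection is to what the article states, an unseen analysis plan would not excuse it.

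The loss of the primary measurement is conditional on reading removal as leaving the trial. Its size cannot be computed from the protocol and is probably small. With one patient lost from an active arm, power stays at 96.1% or above on the planned means and SD, and the illustrative shift is at most 8% of the smallest planned difference from sham before weighting by the chance of an event.

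The case for change therefore rests on one clear instruction and a minimal unblinding rule, not on bias. It is a low-severity improvement.

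**What to change.** In the section on randomization and blinding, replace the sentence on serious adverse events with:

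> *After a serious adverse event, stimulation is stopped. The code is opened only if knowing the allocation is needed for the patient's care, and the outcome assessor stays blinded. Where the patient is able and willing, the scheduled post-evaluation is still done and the patient is kept in the assigned group.*

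In the section on safety and adverse effects, add that for serious events stimulation stops at once under this rule, and that reporting to the principal investigator and ethics committee, and their joint review, continue as written. The joint review should not be withdrawn for serious events. The Withdrawals section needs no change.

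The cost is minor rewording plus the ethics committee review that the article already requires for protocol modifications. The stop of stimulation is kept, and no patients, visits or procedures are added. Recruitment was planned for January to December 2023; if conduct is complete, the report can still state which rule was applied and keep any affected patient in the assigned group.
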